## Abstract

**Background:**

Salmonella Typhi is responsible for about 20 million episodes of illness and over 140,000 deaths annually globally. South Asia has the highest documented burden of typhoid and is home to the multi-drug resistant H58 strain that makes treatment more challenging. The WHO recommends the use of Typhoid Conjugate Vaccines in typhoid endemic countries. Decisions on the preferred immunization strategy should be based on an analysis of disease burden, availability, affordability, and operational feasibility. Typhoid vaccines have so far remained unimplemented as public health measures because of a perceived decline in typhoid burden in recent years. The apparent decline, based on hospital reports, may be a result of rampant antimicrobial use in the community and therefore estimation of disease incidence at the community is necessary to better measure disease incidence and transmission.

**Methods:**

Age-specific incidence of typhoid fever in children between 6 months and 15 years will be estimated in four community based cohorts in varied settings across India using standardized protocols for active fever surveillance in the community. Data will be collected on secured cloud infrastructure using a combination of android and web-based real-time data collection tools. Blood cultures will be done for children with fever lasting 3 or more consecutive days using automated blood culture systems. Those with blood-culture confirmed typhoid fever will be followed up till 90 days to estimate costs and clinical outcomes of the illness episodes. Environmental factors, access to safe water, sanitation, hygiene, food hygiene, demography, population density and socioeconomic status will be assessed periodically to characterise risk factors and permit extrapolation of burden to similar risk settings.

**Discussion:**

With the availability of licensed typhoid conjugated vaccines in India, it is important to consider whether the burden of disease is present and sufficient to require the use of vaccine in addition to other interventions. Active case finding in the community permits the detection of cases that would be missed in facility-based surveillance systems. Understanding the age distribution, burden, cost-of-illness and transmission of disease is essential to plan interventions and predict their potential impact.

**Trial registration:**

The surveillance has been prospectively registered in the Clinical Trial Registry of India (CTRI/2017/09/009719) on 12 September 2017.

## Background

Salmonella Typhi is the leading cause of enteric fever cases responsible for between 12 and 21 million illness episodes and over 140,000 deaths each year globally [1, 2]. The disease is largely prevalent in the low and middle income countries of South Asia. Three community-based cohort studies conducted between 1995 and 2006 in India estimated the incidence of culture confirmed typhoid at 377 (178–801) per 100,000 person years with the highest incidence in early childhood [3–5]. The burden of enteric fever is predicted to worsen with the emergence of multi-drug resistant strain H58 in this region.

The World Health Organization (WHO) in its position paper on typhoid published in 2008 [6] recommends the use of typhoid vaccines to prevent infection in high-risk populations, particularly where antibiotic resistance is prevalent. These recommendations have remained unimplemented in India partly due to a perceived decline in the incidence and severity of typhoid fever in recent hospital-based reports accompanied with evidence of heterogeneous distribution of disease. These findings of declining disease burden in hospital based studies can partly be attributed to the indiscriminate early use of antibiotics to treat febrile illness. Newer antibiotics, that are increasingly accessible over the counter, have been shown to decrease transmission of this host-restricted organism when administered appropriately, early in disease [7–9]. Furthermore, antibiotics decrease culture confirmation by achieving defervescence in ambulatory care where cultures are generally not performed and by decreasing the sensitivity of blood culture post antibiotic therapy. In the absence of an alternative diagnostic assay of sufficient diagnostic accuracy, estimation of disease burden continues to rely on isolation of the organism by blood culture that is likely to be influenced by prior treatment and healthcare seeking behaviour.

While it is challenging to disaggregate the complex interplay between antimicrobial use, antimicrobial susceptibility and disease burden, estimating age-specific incidence of typhoid in the community by investigating febrile episodes prior to antimicrobial therapy will provide a better understanding of current disease burden and its transmission dynamics.

Estimating the burden of disease in children who are the most likely beneficiaries of typhoid conjugate vaccines in national immunization programs will permit us to predict the potential utility of such a vaccine introduction. In this study we will estimate the risk of developing typhoid in cohorts of children aged between 6 months and 15 years through active weekly surveillance for suspected typhoid fever. This approach will permit us to identify febrile illness episodes, document antimicrobial use and ensure blood culture prior to antimicrobial therapy in those with suspected typhoid fever.

## Methods

### Hypothesis

Active, community-based surveillance will estimate the true incidence of typhoid fever and provide a better understanding of transmission of typhoid in the population than available data from hospital based extrapolations.

#### Objectives

The two-fold objectives of this multi-site active surveillance are as followsTo estimate the age specific incidence of culture confirmed typhoid fever in 6 months-4 years, 5–9 and 10–14 years age groups across four geographically distinct sites in IndiaTo describe the incidence of acute febrile illness and its associated treatment practices in the community

#### Inclusion and exclusion criteria

##### Inclusion criteria

A child between 6 months and 13 years + 364 days of age.A child who is likely to remain in the study area for the duration of the study.

##### Exclusion criteria

Non-consent

### Study design

We will recruit 6000 eligible children from each of the four geographically distinct study sites across India. Children are eligible to participate if they are between 6 months and 13 years + 364 days of age, likely to be in the study area for the duration of the study and are willing to receive investigations in the event of febrile illness. All eligible children living in the designated study area will be offered participation and the enrolment will continue till 6000 children have been recruited into each site’s cohort. If multiple eligible children are present within a household, all of them will be eligible to participate. Written informed consent will be obtained from the primary caregiver in addition to assent from age-eligible children.

Active weekly fever surveillance will be performed by trained study personnel either through home visits or by telephonic contacts through the course of study participation. Each participant will be followed for 24 months or until the child attains 15 years of age, whichever is earlier. The study team will ensure at least one face to face contact with the child and the primary care giver every 4 weeks. During these weekly contacts, details of any illness, visits to a health facility and treatment received since the previous visit will be recorded for each participant within the household. If contact with the parents/primary caregiver is not established for two consecutive weeks, then a supervisory visit will be made to confirm that the child is unavailable for surveillance. Parents are encouraged to report any fever episode to the study team at the earliest in addition to reporting them at weekly visits by study personnel.

In the event of fever, a daily follow up will be established until there are three consecutive fever free days. A digital thermometer and a fever diary card will be provided, and primary caregivers will be trained to use the thermometer and document the temperature three times a day. The study team will also document the temperature of the child in the fever diary card during home visits. At each daily contact during the fever follow up, the study team will document information pertaining to the previous calendar day including the highest documented temperature. If the child has any serious illness the parents will be encouraged to seek healthcare from their preferred provider. The family will be informed the need to avoid antibiotics and over the counter medicines that are not prescribed by their physician.

Any reported fever for 3 or more consecutive days will be designated as ‘Suspected Typhoid Fever’ and the child will be encouraged to visit the study clinic. At the study clinic the child will be evaluated by a study physician on the fourth day of fever and if there is history of fever in the preceding 12 h a blood culture will be requested. If the child has been afebrile for over 12 h, unless clinically indicated the blood culture will be deferred. Any subsequent fever within the next 24 h will warrant a blood culture. Prior antimicrobial therapy will not be a contraindication for blood culture. If a child has received a blood culture in the previous 14 days, blood culture will be withheld unless it is requested for by the clinician treating the participant.

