## Discussion

Efficacious, licensed conjugate typhoid vaccine are currently available in India [11, 12]. Uncertainty about disease burden and distribution fueled by hospital-based literature suggesting declining burden in recent years has hindered the adoption of typhoid vaccines as a public health intervention [13, 14]. Examining the incidence, age distribution and transmission dynamics of typhoid fever through active surveillance studies in geographically distinct sites will enable us to uncover disease that remains undetected in hospital-based reports because of varying health seeking characteristics and the rampant use of antibiotic early in febrile illness prior to seeking healthcare in facilitates that perform appropriate diagnostics. Persisting transmission of typhoid in the communities where indiscriminate antibiotic use is rampant may lead to the emergence of multi-drug resistant typhoid haplotypes that will be increasing challenging to treat [15, 16].

The age distribution of typhoid not only indicates the force of infection but also enables policy makers to make informed decisions on the choice and timing of vaccines interventions. Multi-site, multi-year examination of incidence of typhoid is needed to ascertain whether targeted control strategies are more appropriate than universal immunization.

Active surveillance systems using blood culture for identifying cause of fever face several challenges. In the absence of point of care diagnostics with acceptable diagnostic accuracy, this surveillance will perform automated blood cultures on children with suspected typhoid fever. This process requires the aseptic collection of 3 to 5 ml of blood in febrile episodes, preferably before initiation of antibiotics. We propose a blood culture in those with three or more days of reported fever as the prevalence of antibiotic therapy in those with over 3 days of fever is substantial. We use reported fever over documented temperature as temperature documentation for fever has been inconsistent in prior studies in these population and may result in several suspected typhoid fevers remaining ineligible for culture.

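### Objective 2 describes community treatment of fever in families whom the study itself advises against unprescribed medicines, so recorded unprescribed use will probably fall below usual practice

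*Protocol article*

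**What the plan says.** The Objectives section gives two aims. The second has two parts: how often acute febrile illness occurs, and how it is treated in the community.

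The treatment data come from the cohort itself. Under Study design, at the weekly contacts "details of any illness, visits to a health facility and treatment received since the previous visit will be recorded for each participant". The Background adds that the surveillance is meant to "identify febrile illness episodes, document antimicrobial use and ensure blood culture prior to antimicrobial therapy in those with suspected typhoid fever".

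The fever follow-up paragraph of Study design begins: "In the event of fever, a daily follow up will be established until there are three consecutive fever free days". The same paragraph contains the advice to families: "The family will be informed the need to avoid antibiotics and over the counter medicines that are not prescribed by their physician". Two other procedures in Study design bear on treatment. For early reporting, "Parents are encouraged to report any fever episode to the study team at the earliest". Once fever has lasted three or more days, "the child will be encouraged to visit the study clinic", where a study physician evaluates the child.

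The Discussion gives, as one reason why hospital reports miss disease, the "rampant use of antibiotic early in febrile illness prior to seeking healthcare" in facilities able to make the diagnosis. The Background mentions easy over-the-counter access to newer antibiotics.

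**The concern.** The families who supply the treatment data are also told by the study to change part of the behaviour being described. Antibiotics taken without prescription are one component of the early antibiotic use that the protocol regards as typical of these communities. The advice is aimed at that component.

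At stake is the meaning of the treatment-practice half of objective 2. A figure for unprescribed use taken from these fevers describes families under active surveillance and advice. If it is reported as ordinary community practice, a low value could be read as showing that self-medication is uncommon, when it may partly show that the study's advice was followed. The article describes no other source for usual practice, such as a survey before surveillance began or a group not given the advice, and it does not mention that the advice could alter what is being measured.

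**Working it through.** The plan states no figure on this point, so there is nothing to reproduce. The Sample size section concerns typhoid incidence only. The check sets the passages side by side.

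1. **What is to be described.** Treatment practices for febrile illness in the community (Objectives).
2. **Who supplies the data.** Enrolled children, through weekly contacts (Study design). No second source is described.
3. **Who receives the advice.** The families of the same children, in the paragraph on fever follow-up (Study design). All eligible children in a household may enrol, so advice given during one child's fever also reaches any enrolled siblings.
4. **What the advice covers.** Antibiotics and over-the-counter medicines without a physician's prescription. Prescribed treatment is not discouraged.
5. **What else acts on treatment.** Early reporting shortens the part of an illness that precedes study contact. Longer fevers are directed to a study physician. The effect of this on prescribed antibiotics could go either way, and the text does not settle it.
6. **What escapes the advice.** Medicines started before the study team's first contact, in a fever that occurs before the household has received the advice. The article does not separate this group.

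The direction for unprescribed use can be written down. Let p be the share of fevers treated with an unprescribed medicine under usual practice, f the fraction of those treatment decisions taken after the family has been advised, and r the relative reduction that the advice produces. Then

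recorded share = p × (1 − f × r).

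For any f and r above 0 this lies below p. If families also under-report what they were told to avoid, the recorded share falls further. If f or r is 0, there is no bias from the advice. The documents give no value for p, f or r, so no percentage can be attached.

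Two results are outside this argument. Counting febrile episodes does not depend on which medicine was taken. For objective 1, the advice serves the stated aim of taking the culture before antimicrobials.

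**The case against.** The best case on the other side has five parts.

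- **Some reactivity is unavoidable.** Any active surveillance alters behaviour to some degree, and here the advice supports the primary aim. This stands as a reason to keep the advice. It does not justify leaving the resulting data unlabelled.
- **Timing may already be captured.** Weekly contacts record treatment since the last visit, and daily contacts during fever cover the previous calendar day. This stands in part. Treatment reported when a fever first comes to light at a weekly contact must precede the follow-up of that fever. The article does not list treatment among the daily items, however, and does not place a medicine's start relative to first contact.
- **The analysis may be specified elsewhere.** The Data analysis section covers incidence rates only and sets out no treatment-practice analysis, pooled or otherwise. A reader might infer that pooling all fevers is planned; the article does not say so. Its silence is not the fault raised here. The point rests on a stated objective and a stated procedure that pull against each other.
- **Only part of the practice of interest is touched.** Early antibiotics prescribed by local practitioners also fit the protocol's account, and the advice leaves them alone. This stands and limits the point to unprescribed and over-the-counter use.
- **Pre-contact treatment has its own bias.** It is cut short by how quickly parents report and omits medicines started later in the illness. This also stands, and it is why pre-contact treatment should not be the sole main estimate.

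**Conclusion.** The point holds for the treatment-practice half of objective 2. As planned, recorded unprescribed antibiotic and over-the-counter use will probably understate usual community practice. This assumes that at least some families heed the advice or under-report what they were told to avoid. The size is unknown.

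Two stronger readings are tempting but unsupported. A reader might infer that the advice is given afresh at every fever, so that the distortion builds over the 24 months of follow-up. The sentence stands in the fever follow-up paragraph, but the text does not say that the advice is repeated, and nothing shows a growing bias. Even if given once, the advice could carry over to later fevers.

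A reader might also infer that the data could not support the protocol's argument about widespread community antibiotic use. That does not follow. With a downward bias, high recorded unprescribed use would support the argument all the more strongly; only low recorded use would be ambiguous.

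This is a worthwhile, inexpensive improvement to one descriptive objective. It implies no judgement against giving the advice.

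**What to change.** Keep the advice, and change what is recorded and how it is reported.

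- **Recording.** At the existing contacts, note for each medicine whether it was prescribed and whether it was started before or after the study team's first contact in that episode. Note when each household first received the advice.
- **Reporting.** Present pre-contact and post-contact treatment separately, and separate fevers before and after the household was first advised. The split should be by household, not by child, because siblings can be enrolled together.
- **Labelling.** Describe post-contact treatment, and all fevers after first advice, as practice under surveillance and advice. Interpret overall unprescribed use as a likely lower bound on usual practice.
- **Main presentation.** Show the pre-contact figure beside the whole-episode figure, without replacing it.

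The cost is about one extra field on an existing form, a few sentences in the analysis section, and smaller numbers in each stratum. The timing should be captured from the start, since it may be hard to recover later. Consent and weekly contact may themselves shift behaviour before any fever, so the change reduces the problem and makes it visible but does not remove it.

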### Laboratory methods

A dedicated laboratory team will be present at each site for collection of blood samples and subsequent processing using automated blood culture systems using standard operating procedures across sites. For children between 6 months and 1 year, 3 mL will be inoculated into a paediatric blood culture bottle. For children above 1 year of age, 5 mL of blood will be inoculated into a paediatric blood culture bottle. Additional blood may be drawn for investigations requested by the treating physician. The total volume of blood drawn must not exceed 2 mL per kg body weight. Blood samples will be transferred to the site laboratory facility within 4 h of sample collection at ambient temperature. Where blood cultures do not provide a definite diagnosis and fever persists for 7 or more days, additional serology based tests may be performed as clinically indicated but these will not contribute to the estimates of typhoid incidence. *S.* Typhi isolated from other normally sterile sites will also contribute to confirmed typhoid fever estimates. All typhoid isolates will undergo antimicrobial susceptibility testing and will be archived for future genomic characterisation. All other significant culture isolates including *S. Paratyphi* will be documented.

### Sample size

The incidence of acute typhoid fever in children aged 6 months to 15 years in India was previously estimated to be between 6 and 12 per 1000 child years (CY) with the highest rates in 1–4 year olds [4, 10]. If community-level incidence has declined as hospital-based estimate suggest, the current incidence in this age-group would be between 1 and 5 per 1000 CY. Recruiting, at each site, a cohort of 5600 children between 6 months and 13 years + 364 days will provide 8400 child years of observation over 18 months that would be distributed approximately as 2400 child years in the 6-month to 4 years, and 3000 child years in the 5–10 and 11–14 age groups in an open cohort and assuming a uniform death rate. Accumulating 8400 child-years will exclude an incidence rate of 2/1000 with 95% confidence if there are 26 or more cases (IR > 3/1000) in the cohort. In turn, this sample size will be adequate to exclude at 95% confidence limits, a rate of 2/1000 in each of the 6 months-4 years, 5–10 and 11–14 years age groups in which the observed incidence is 4/1000 or greater using a Fishers exact test based on the formula (Armitage,1971; Snedecor & Cochran,1965) as described in Epidemiologic Analysis with a Programmable Calculator, 1979.

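### The sample-size section rests on 5600 children for 18 months (8400 child-years per site), the design on 6000 children for 24 months, so the stated person-time, 26-case figure and precision do not describe the study as designed

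*Protocol article*

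**What the plan says.** Three sections of the protocol article bear on person-time per site.

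- **Sample size.** The starting point is "Recruiting, at each site, a cohort of 5600 children between 6 months and 13 years + 364 days", which "will provide 8400 child years of observation over 18 months". These are split into about 2400 child-years in the youngest age band and 3000 in each of the other two, "in an open cohort and assuming a uniform death rate". The precision statement follows: "Accumulating 8400 child-years will exclude an incidence rate of 2/1000 with 95% confidence if there are 26 or more cases (IR > 3/1000"). A second statement covers the age bands, for those "age groups in which the observed incidence is 4/1000 or greater using a Fishers exact test".
- **Study design.** "We will recruit 6000 eligible children from each of the four geographically distinct study sites across India", with enrolment continuing until that number is reached. Then: "Each participant will be followed for 24 months or until the child attains 15 years of age, whichever is earlier".
- **Data analysis.** This section refers to a two-year study period. It computes rates over person-time actually observed and at risk, leaving out time with illness and time not under surveillance.

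The article does not call 8400 a net figure after attrition, does not call 18 months an average or an interim point, and gives no loss rate.

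**The concern.** Both planning inputs differ between sections: 5600 against 6000 children, and 18 against 24 months. The case count needed to exclude a fixed rate grows with person-time, so a count derived for 8400 child-years cannot be carried over to a substantially larger denominator.

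What is at stake is whether the sample-size justification belongs to the study being run. Someone checking a site's completed follow-up against the printed count would have the wrong number, and someone judging the planned precision would see it understated. The age-band figures share the problem, since 2400 + 3000 + 3000 = 8400.

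**Working it through.** **Inputs.** From Sample size: 5600 children, 18 months, 8400 child-years, 26 cases, reference rate 2/1000, 95% confidence (sidedness not stated). From Study design: 6000 children, 24 months, cap at age 15, entry from 6 months to just under 14 years.

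**Step 1: reproduce the plan's figures.** 5600 × 1.5 = 8400 child-years, an exact match, so the product contains no allowance for loss within the 18 months. The exact two-sided 95% Poisson lower limit for x cases in T child-years is χ²(0.025; 2x) / (2T).

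- x = 26, T = 8400: rate 3.10/1000, 95% interval 2.02 to 4.54. This excludes 2/1000.
- x = 25, T = 8400: lower limit 1.93/1000. This does not.

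So 26 is the exact two-sided minimum at 8400 child-years, and the plan's arithmetic is correct on its own inputs.

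**Step 2: person-time under the design.** The ceiling is 6000 × 2 = 12,000 child-years. For the age-15 cap, assume entry ages uniform from 0.5 to 14 years, a range of 13.5 years. Children entering before 13 contribute 2 years each. Those entering between 13 and 14 contribute 1.5 years on average. This gives 6000 × (12.5/13.5 × 2 + 1/13.5 × 1.5) = 11,778 child-years before any loss or excluded time.

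**Step 3: how far does 26 carry?** Setting the lower limit for 26 cases equal to 0.002 gives T = 8,492 child-years. Beyond that, 26 cases no longer exclude 2/1000 on the exact two-sided limit. On a one-sided exact limit the break-even is 9,109.

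| Basis | Child-years | Rate at 26 cases (/1000) | Lower 95% limit (/1000) | Exact minimum cases |
|---|---|---|---|---|
| 5600 × 1.5 y | 8,400 | 3.10 | 2.02 | 26 |
| 6000 × 1.5 y | 9,000 | 2.89 | 1.89 | 28 |
| 5600 × 2 y | 11,200 | 2.32 | 1.52 | 33 |
| 6000 × 2 y, capped at 15 | 11,778 | 2.21 | 1.44 | 35 |
| 6000 × 2 y, ceiling | 12,000 | 2.17 | 1.42 | 35 |

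Correcting either input alone is enough to move the figure. Across exact one- and two-sided, mid-P, Byar, Wald, log and score limits, the minimum at 12,000 child-years lies between 33 and 36.

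**Step 4: how much lost time would bring 26 back?** 1 − 8,492/12,000 = 29% of the ceiling, or 1 − 8,492/11,778 = 28% of the capped figure.

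**Step 5: effect on precision.** Probability that the exact lower limit exceeds 2/1000:

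| True rate | 8,400 CY (26 cases) | 12,000 CY (35 cases) |
|---|---|---|
| 3/1000 | 0.46 | 0.59 |
| 4/1000 | 0.92 | 0.98 |

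The design as written does better than the sample-size section claims.

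**The case against.** The best defence is that the 26-case statement is conditional on 8400 child-years and correct there. The article nowhere applies it to 24-month data. The rate printed beside it, above 3/1000, also guards against misuse, because it stays sufficient as person-time grows. It requires more than 0.003 × 9,000 = 27, so 28 cases (exact minimum 28). At 11,200 it requires 34 (minimum 33), at 11,778 it requires 36 (minimum 35), and at 12,000 it requires 37 (minimum 35). All of this stands.

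A reader might therefore be tempted to infer that the study will wrongly declare 2/1000 excluded. In support, one could note that at a true rate of 2/1000 the chance of 26 or more cases is 2.2% at 8,400 child-years but 33% at 11,778. The documents do not support that inference. It detaches the count from its stated denominator and from its companion rate. The objectives are to estimate and describe incidence, and Data analysis uses actual person-time with no case-count rule. Nor is 26 the only threshold, since 4/1000 is given for the age bands.

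It is also fair to say that the person-time to be accrued is unknown. Loss, illness time and gaps in surveillance all reduce it, and a reduction of 28 to 29% would make 26 adequate. A condensed article may leave the loss allowance to the full protocol, so its absence is not held against the plan. What this does not answer is that the article prints two incompatible cohort sizes and follow-up periods, and that 8400 is exactly 5600 × 1.5 and is presented as such.

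**Conclusion.** The inconsistency is real. The per-site person-time, case count and precision in the sample-size section belong to 5600 children over 18 months, whereas the design and analysis sections describe 6000 children over two years. The error lies in the unreconciled inputs and not in the calculation.

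On the design as written, person-time is at most 12,000 child-years, and at 11,000 to 12,000 the exact minimum is 33 to 35 cases instead of 26. These counts assume a two-sided exact Poisson limit. The 11,778 figure also assumes uniform entry age, no loss and no excluded time.

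The direction is favourable: precision is understated and the study is not underpowered. Recruitment, follow-up and the planned estimates are unaffected. Severity is minor to moderate.

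**What to change.** 1. Reconcile Study design, Sample size and Data analysis on one cohort size and one follow-up period.
2. State how 8400 child-years relates to them. If it is a minimum after attrition, say so and give the loss assumed. If 18 months is intended, change the 24-month and two-year statements to match.
3. Restate the criterion for the resulting person-time, preferably as an exact two-sided 95% lower limit above 2/1000 at the child-years actually accrued. Show case counts only as illustrations under stated loss assumptions, for example 26 at 8,400, 33 at 11,200 and 35 at 12,000 child-years.
4. Recompute the age-band child-years and the 4/1000 statement on the same basis.

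The cost is wording and arithmetic, unless the sponsor decides that 18 months or 5600 children is what is meant, in which case the design text changes instead.
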